## Abstract

**Background:**

Dutch construction workers are offered periodic health examinations. This care can be improved by tailoring this workers health surveillance (WHS) to the demands of the job and adjust the preventive actions to the specific health risks of a worker in a particular job. To improve the quality of the WHS for construction workers and stimulate relevant job-specific preventive actions by the occupational physician, we have developed a job-specific WHS. The job-specific WHS consists of modules assessing both physical and psychological requirements. The selected measurement instruments chosen, are based on their appropriateness to measure the workers' capacity and health requirements. They include a questionnaire and biometrical tests, and physical performance tests that measure physical functional capabilities. Furthermore, our job-specific WHS provides occupational physicians with a protocol to increase the worker-behavioural effectiveness of their counselling and to stimulate job-specific preventive actions. The objective of this paper is to describe and clarify our study to evaluate the behavioural effects of this job-specific WHS on workers and occupational physicians.

**Methods/Design:**

The ongoing study of bricklayers and supervisors is a nonrandomised trial to compare the outcome of an intervention (job-specific WHS) group (n = 206) with that of a control (WHS) group (n = 206). The study includes a three-month follow-up. The primary outcome measure is the proportion of participants who have undertaken one or more of the preventive actions advised by their occupational physician in the three months after attending the WHS. A process evaluation will be carried out to determine context, reach, dose delivered, dose received, fidelity, and satisfaction. The present study is in accordance with the TREND Statement.

**Discussion:**

This study will allow an evaluation of the behaviour of both the workers and occupational physician regarding the preventive actions undertaken by them within the scope of a job-specific WHS.

**Trial registration:**

NTR3012

## Background

Dutch construction workers are offered periodic health examinations in order to detect risk factors for work-related diseases and changes in health. If necessary, preventive actions can be taken to prevent deterioration of their health status and to improve work functioning. This care can be improved by tailoring workers' health surveillance (WHS) to the demands of the job and adjusting the intervention measures to the specific needs associated with particular jobs. To improve the quality of the WHS for construction workers and to increase recommendations of job-specific intervention measures by occupational physicians (OPs), we developed a job-specific WHS. The rationale for developing job-specific WHS for construction workers is based on the consideration that the aims and content of the WHS and proposed interventions should be tailored to the occupation of interest.

The goals of WHS are as follows: (i) to prevent the onset, recurrence and/or worsening of work-related diseases; (ii) to monitor and promote individuals' health in relation to work; and (iii) to monitor and promote work functioning and deployment [1]. Accordingly, each WHS is designed in such a way that it is relevant to the nature of the demands and health effects of the occupation of interest [2]. Evidence from the literature supports the perception that a bricklayer has a physically demanding occupation whereas the construction supervisor has a mentally demanding occupation. A systematic review of the literature revealed details on the work demands and health effects of both occupations [3]. These details suggest that a fruitful approach would be to develop and implement a job-specific WHS for construction occupations aimed at the demands and health effects associated with the work.

The screening instruments selected for the WHS should be attuned to the physical and psychological requirements of the job. Several authors have argued the relevance of job-specific measurement instruments. For example, Tufts et al. [4] explicate the need for tests measuring auditory fitness for duty. Other examples are the trucker strain monitor for measuring psychological job strain in truck drivers [5,6], a functional capacity evaluation for hospital nurses [7] and the fire fighting simulation test for fire fighters [8]. The current instruments used in the Dutch WHS for construction workers are lacking such an approach.

A job-specific WHS should incorporate job-specific (and preferably evidence-based) intervention measures. A job-specific occupational health education program for preventing work-related musculoskeletal back injuries in construction labourers, for example, has proven to be effective [9]. Other examples of recommendable job-specific interventions for bricklayers are the use of a scaffolding console to reduce the frequency and duration of trunk flexion during bricklaying [10,11] and the use of mechanised transport to reduce the frequency of handling objects [10]. A structured protocol for advising and counselling OPs on job-specific intervention measures does not exist in the Netherlands. Such a protocol could facilitate the recommendation of preventive actions by OPs.

In the present paper, we refer to the bricklayers and supervisors participating in the study as 'workers', in order to distinguish them from the other participants in the trial: OPs, ergonomists and physician's assistants.

### Objectives

We hypothesise that the job-specific WHS will influence workers who attend it to undertake preventive actions. Moreover, we hypothesise that based on the job-specific WHS, OPs will advise more preventive actions in total and more job-specific (compared with general health) preventive actions. The objective of this paper is to describe the study protocol used to evaluate the job-specific WHS and to test these hypotheses.

## Methods/design

### Dutch context

In the Netherlands, employers are obliged to offer their employees a medical examination, as stated in Article 18 of the Dutch Working Circumstances and Occupational Health and Safety Act [12]. Employees in the construction industry are invited for such a medical examination once in every four years (when they are under the age of 40) or every two years (when they are over 40 years old). This examination is part of their collective labour agreement. Arbouw (the Health and Safety Institute for the Dutch construction industry) provides this service for all employees in the construction industry. Employees are invited to an Occupational Health Service (OHS) near their place of residence. Attending the periodic medical examination is voluntarily. At the time this study was prepared, the attendance rate was 47% [13]. In the collective labour agreement of the workers is recorded that 1) research is performed at the OHS under the authority of Arbouw and 2) the information collected during the medical examinations can be used for research purposes. When attending their medical examination the workers are reminded in writing of this agreement and they can choose whether or not to participate voluntarily. The workers are aware of the fact that by participating they give the researchers written consent to use their information anonymously for research purposes.

### Study design

In the following description of the design of this study we follow the TREND Statement [14]. The primary objective of the study is to compare how attending a job-specific WHS versus the current WHS (care as usual, CAU) influences the preventive actions undertaken by bricklayers and supervisors (hereafter referred to as 'workers'). Our hypothesis is that the job-specific WHS helps bricklayers and supervisors undertake preventive actions.

Offices of one OHS participate in the study. At the offices of the OHS in the control group, the workers attend CAU. The OPs in the control group counsel their workers according to CAU. Workers in the intervention group attend the job-specific WHS, and the OPs in the intervention group counsel their workers according to the job-specific protocol. After inclusion and baseline measurements, measurements take place at two and three months after baseline. The medical ethics committee of the institution, the Academic Medical Center, approves the present study, and the board of the participating OHS advises positively about the local feasibility of the study.

Blinding of the OPs, physician's assistants, ergonomists or workers is not feasible for several reasons. The workers are familiar with CAU as they are invited regularly (every four or two years) for their WHS. Any modification to the standard procedure would be noticed. Moreover, every OP is trained to apply either the experimental intervention (job-specific WHS) or CAU. Therefore, all the OPs know which type of intervention they perform. To prevent contamination between the two groups, the OPs in the control group will neither be informed about nor receive training in the job-specific WHS. The OPs in the intervention group are requested not to disclose the new intervention during the length of the study to the OPs in the control group. Furthermore, the chance of contamination is small as the OPs in the intervention group work at different offices than the control group. The physician's assistants will be informed about the procedural changes in the job-specific WHS compared to CAU. The ergonomists will be trained to apply the experimental intervention only, as they do not contribute to the CAU.

### Study population and recruitment

The research population includes all workers with the occupation bricklayer or supervisor who are invited by the OHS. Workers are eligible to participate when they are i) primarily working as a bricklayer or construction supervisor; ii) male; iii) able to read, speak and write Dutch sufficiently well and iv) not planning to leave their occupation in the three months after inclusion due to resignation or (early) retirement. Because both occupations consist primarily of men, we include only men.

The study population is recruited through the participating OHS. The workers, who are invited at the offices where the job-specific WHS is implemented, are informed by a letter about the innovation at their OHS. Then, concurrent procedures are performed for both the control and intervention groups: all workers are asked to confirm their attendance, and if necessary, another date or time is arranged. When a worker does not show up without cancelling, the OHS will try to follow-up by phone to make a new appointment if desired by the worker.

### Recruitment of occupational physicians

Participating OPs are recruited between October and December 2011 from offices of the same OHS. These offices are geographically widespread over the Netherlands and were selected on the basis of i) the number of bricklayers and supervisors expected to be invited for a WHS in 2012 and, for the intervention group, ii) the possibility of setting up a job-specific WHS. To provide a safe testing situation, the office must have a covered accommodation of approximately 15 × 15 m and the ability to set a 7 m ladder up against the building.

### Intervention

The Dutch Guideline for Workers' Health Surveillance for the Occupational Physician [1] was followed in the process of developing the job-specific workers' health surveillance (WHS) program. The content of the job-specific WHS was determined in a step-by-step procedure partially based on Bos et al. [15]. The job-specific WHS aims at detecting signals of work-related health problems, reduced work capacity and/or reduced work functioning. The worker fills in a job-specific questionnaire consisting of validated and reliable screening instruments, then biometry measurements are carried out by a physician's assistant, and subsequently the worker performs physical performance tests under the guidance of an ergonomist. The OP uses a structured protocol to assess the results and to prepare the consultation with the worker. Thereafter, the OP discusses the results of the job-specific WHS and recommends desirable preventive actions to the worker in a 20-minute consultation. Together with the worker, a course of action is drawn up and a follow-up appointment is arranged within eight weeks after the job-specific WHS, if necessary. A structured intervention protocol for the OP facilitates job-specific intervention measures and an evaluation of the actions undertaken by the worker. The worker receives a report with the advises of the OP. In the job-specific WHS the following domains are represented: musculoskeletal system, safety (vision, perception of sound, psychological vigilance and working at heights), hazardous substances (skin, lungs), health in relation to work (cardiometabolic health) and work ability.

In Table 1, an overview of the domains and content of the job-specific WHS for both occupations is given. The development and the exact content of the job-specific WHS is described in Additional file 1.

**Table 1 T1:** Overview of the requirements and content of the job-specific workers' health surveillance programs for the two occupations.

Requirements	Instruments
**Physical requirements**	Signalling questions and physical performance tests that -- when possible -- measure combined physical requirements:

*both occupations:*	*both occupations:*
Climbing stairs	Climbing stairs (2 × 6 times)
Climbing a ladder/scaffold	Climbing a ladder (7 m)

*bricklayers only:*	*bricklayers only:*
Standing	Signalling questions hand-arm vibration syndrome [19]
Repetitive movements	Bricklaying test (mixing a mortar-like substance, repetitive hand-arm movements with a trowel, picking up and laying bricks at several heights, lifting and carrying 25-kg sacks)
Working above shoulders	
Working with a bent back	
Squatting and kneeling	
Lifting and carrying (25 kg)	

*supervisors only:*	*supervisors only:*
Walking	Walking 10 min

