### Care as usual

CAU aims at detecting signals of work-related health problems and risk factors. The worker fills in a questionnaire and a physician's assistant carries out biometry measurements. The biometry measurements of both the job-specific WHS and CAU are identical. The questionnaire covers several topics including health, perceptions of work and risk factors at work. Neither scale scores nor cut-off points are calculated, except for work ability. The questionnaire used in CAU is identical for all occupations, and no protocol exists for analysing the results. The OP discusses the results of both the biometry and the questionnaire with the worker in a 20-minute consultation. No structured protocol exists to facilitate the OP in their counselling. A report of the results is sent to the home address of the worker afterwards.

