#### Sample size and assignment

The sample size is based on detecting a difference in activities or interventions undertaken by the worker in the six months after they have attended their WHS. No information on this is available from literature. From the registered activities and interventions in the Arbouw-database, we expect 10% of the workers in the control group to undertake an activity registered by the OP. We have decided that an absolute increase of 20% in interventions undertaken by the workers is a relevant difference. For an increase of 20% (from 10 to 30%) with alpha 0.05 (two-tailed) and a power of (1-beta) = 0.80, power calculation using the Nquery Advisor software results in 75 workers per group. However, we expect a small effect at the level of the OP (ICC = 0.01). Every OP will treat ~15 workers. This results in a design effect of 1.14 ((1+(N-1)*ICC) and an adjusted sample size of 86 per group, divided over at least 6 OPs [16]. With an expected loss to follow-up of 20% and an initial attendance of 50% at the OHS, we must invite 206 workers per group (103 bricklayers, 103 supervisors).

We do not expect major differences between the various offices of a single coordinating OHS. No restrictions or matching criteria were imposed.

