### Statistical analysis

The baseline data and the primary and secondary parameters will be presented using descriptive statistics. The following characteristics at baseline will be compared between the intervention and control groups: occupation, work experience in years in construction and in the current occupation, work hours per week and any possible worker compensations such as early retirement or partial disability. Furthermore, these characteristics will be compared overall and by study condition in those lost to follow-up and those retained. Moreover, the age and occupation of the study population at baseline and target population (all invited by the OHS) will be compared. Differences in continuous outcome measures will be tested with an independent samples T-test, differences in proportions will be tested with a Chi-Square test.

The effectiveness of the job-specific WHS on the primary and secondary outcome measures will be analysed on the individual level. First, data for the whole group will be analysed irrespective of the occupation of the worker. Second, subgroup analyses will be performed among the bricklayers and supervisors. For all analyses, a significance level of 0.05 will be applied. Workers with the same OP tend to be more homogeneous than workers with different OPs. Therefore, a two-level logistic regression model with workers at level 1 nested within OPs at level 2 will be used to analyse the binary data. The SPPS Advanced Statistics 19 software will be used to perform the logistic multilevel analysis by using a Generalised Linear Mixed Model (GLMM).

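### The characteristics compared between the nonrandomised groups leave out age and every measured health finding, so unequal need for action would be neither compared nor, as far as stated, adjusted for

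*Protocol article*

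**What the plan says.** The Methods/Design part of the abstract describes a "nonrandomised trial to compare the outcome of an intervention (job-specific WHS) group (n = 206) with that of a control (WHS) group (n = 206". Groups are formed by office of one occupational health service, and under Sample size and assignment the protocol adds: "No restrictions or matching criteria were imposed".

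The Statistical analysis section fixes what is compared between the groups: "The following characteristics at baseline will be compared between the intervention and control groups: occupation, work experience in years in construction". The rest of that list is experience in the current job, weekly hours, and compensations, with early retirement and partial disability as examples. The same list serves for comparing workers lost to follow-up with those retained. Age appears in one other comparison: "the age and occupation of the study population at baseline and target population (all invited by the OHS) will be compared". Binary outcomes go into a two-level logistic model, workers within occupational physicians (OPs), and no covariate is named.

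Two other statements bear on the point:
- Under Intervention: "the OP discusses the results of the job-specific WHS and recommends desirable preventive actions to the worker in a 20-minute consultation".
- Under Care as usual: "The biometry measurements of both the job-specific WHS and CAU are identical".

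The primary outcome takes everyone who attended as its denominator, whatever their need for action.

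**The concern.** Whether a worker is advised to act depends largely on what the examination finds, and the primary outcome counts advised actions that were undertaken. A group with more findings will therefore tend to receive more advice and act more often, whichever programme it attended.

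The groups could differ in this respect for several reasons visible in the protocol:
- The offices are spread over the country, and intervention offices had to meet an extra space requirement.
- Attendance is voluntary, and only workers at intervention offices are told of the innovation by letter before confirming.
- Age is linked to health findings and also to the interval since the last invitation, which is "once in every four years (when they are under the age of 40) or every two years (when they are over 40 years old".

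In a nonrandomised study the listed comparison is the main stated safeguard. Experience and worker compensations are coarse stand-ins for age and health. They do not capture hearing, vision, lung or cardiovascular findings. A model adjusted for every listed characteristic would still leave out age and need for action. The hypothesis that OPs will advise more actions is the most exposed, because advice depends directly on findings.

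**Working it through.** **Step 1: what is listed, set against what is available.**

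| Characteristic | Compared group with group? | Available alike in both groups? |
|---|---|---|
| Occupation, experience, hours, compensations | Yes | Yes |
| Age | No, only study population with all invitees | Yes, since that comparison needs it |
| Biometry findings | Not listed | Yes, stated to be identical |
| Work ability | Not listed | Scored in both; whether the items match is not stated |
| Other questionnaire scores | Not listed | No, care as usual calculates none |

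The gap is therefore in the list and not in the data. Biometry is taken before the consultation, so the OP's counselling cannot have altered it.

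**Step 2: numbers taken from the plan** (Sample size and assignment).
- Attendees per group: 206 × 0.50 = 103.
- Followed up per group: 103 × 0.80 = 82.
- Control rate for the primary outcome: 10%.
- Design effect: 1 + (15 − 1) × 0.01 = 1.14, as the plan states.

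**Step 3: assumptions, none of them in the documents.** There is no true programme effect. A finding is present in 40% of controls and in a share *s* = 50%, 55% or 60% of intervention workers. Workers without a biometry finding can still be advised and act, because advice also rests on the questionnaire.

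**Step 4: expected rates.**
- *Primary outcome.* Let 2% act without a finding. A 10% control rate then requires (0.10 − 0.6 × 0.02) / 0.4 = 22% to act with one. The intervention rate is 0.22*s* + 0.02(1 − *s*) = 12%, 13% or 14%.
- *Advice, strong link (80% advised with a finding, 20% without).* Control: 0.4 × 0.8 + 0.6 × 0.2 = 44%. Intervention: 50%, 53% or 56%.
- *Advice, weak link (60% and 30%).* Control: 0.4 × 0.6 + 0.6 × 0.3 = 42%. Intervention: 45%, 46.5% or 48%.

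**Step 5: false rejection.** For a two-sided 5% normal test with *n* per group and difference *d*, the rejection probability is Φ((d − 1.96·SE₀)/SE₁) + Φ((−d − 1.96·SE₀)/SE₁). SE₀ uses the pooled rate and SE₁ the two separate rates. Example for 10% against 14%, *n* = 82: SE₀ = √(2 × 0.12 × 0.88 / 82) = 0.0508 and SE₁ = 0.0507, giving Φ(−1.17) + Φ(−2.75) = 0.120 + 0.003 = 0.123.

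| Outcome (*n* per group) | False difference, points | Rejection, clustering ignored | Rejection with *n* / 1.14 |
|---|---|---|---|
| Primary (82) | 2, 3, 4 | 6.9%, 9.2%, 12.3% | 6.7%, 8.7%, 11.4% |
| Advised, strong link (103) | 6, 9, 12 | 14%, 25%, 41% | 13%, 23%, 36% |
| Advised, weak link (103) | 3, 4.5, 6 | 7%, 10%, 14% | 7%, 9%, 13% |

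**Step 6: a second set of assumptions.** Let action be strictly proportional to need, with the plan's 86 per group divided by 1.14. Need ratios of 1.25, 1.5 and 2.0 give false differences of 2.5, 5 and 10 points, and rejection in 7.7%, 15.2% and 40.4% of trials. Producing the whole 20-point target difference would take a threefold imbalance.

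**The case against.** The list is not blind to age and health. Partial disability is a coarse health status, early retirement a coarse age marker, and both experience items track age. A reader might infer that only job descriptors are compared, and the text does not support that. What remains is that none of these is a measured finding and that age itself is absent.

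A reader might also infer that an imbalance would go unseen. That is too strong. The Statistical analysis section says baseline data will be described, and the Measurements section says they come partly from the results of both programmes, so an imbalance might show in a table. But no between-group comparison of those data is stated.

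A journal article may leave model covariates to an analysis plan that is not shown, and the text does not say that the model is unadjusted. That is fair: silence on covariates would not be a finding by itself. The comparison list, however, is explicit, and it is the list that is badly chosen.

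The sizes rest on assumed imbalances. All offices belong to one service, and the protocol expects no major differences between them. That is an expectation, and the listed comparison could not check it for age or health.

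Finally, biometry is an imperfect measure of need. It is not itemised for care as usual, and it misses musculoskeletal and psychological needs. This limits how far adjustment can go, but does not justify leaving out what is measured alike.

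**Conclusion.** The point holds as a weakness in the stated between-group list. In an unmatched comparison of offices, age and all measured health findings are left out of the comparison between groups, and no stated adjustment covers them.

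For the primary outcome the consequence is modest under the main assumptions: a false difference of 2 to 4 points against a 20-point target, with rejection in about 7% to 12% of trials (7% to 11% with the design effect). For the proportion advised it is 7% to 41%. The upper end needs both the largest imbalance and the strong link between findings and advice.

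Two further inferences should be resisted. The documents do not show that the groups differ in age or need. Nor do they show that a worker without a biometry finding cannot reach the primary outcome, since advice may also rest on the questionnaire.

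**What to change.** In the Statistical analysis section:

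1. Add age and the biometry findings measured identically in both groups to the list introduced by "The following characteristics at baseline will be compared between the intervention and control groups". Candidates are audiogram, eye test and spirometry, once confirmed as part of the common biometry; one indicator for any abnormal finding would also do. Add baseline work ability if the items match.
2. Apply the extended list to the comparison of workers lost and retained.
3. Report the between-group differences with confidence intervals.
4. Include age and one common biometry indicator as covariates in the two-level models for action undertaken and for advice given.
5. Do not use questionnaire scores that exist only in the intervention group, since they cannot describe both groups in the same way.

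The cost is some wording, a few table rows and a few model terms. No new data collection is needed for age and biometry. Because biometry covers only part of the need for action, residual confounding should still be acknowledged.
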